### Eligibility Criteria

Eligibility criteria were selected to ensure optimal fitness of the study sample with respect to the subsequent implementation of the MS-FIT intervention in the health care setting, to minimize the impact of confounding variables (eg, rehabilitation outcomes), and to ensure comparability with other studies on similar interventions.

#### Inclusion Criteria

The study includes people with a diagnosis of MS according to McDonald’s criteria [31] and aged ≥18 years; all disease courses are eligible (relapsing-remitting, primary progressive, and secondary progressive) [32]. Patients will be included if their disability level based on the Expanded Disability Status Scale (EDSS) [33] is between 2 and 4. Indeed, we expect that in people with MS with a lower EDSS, the proposed intervention might not be effective and other forms of PA based mainly on exercise should be considered. For people with MS with a higher EDSS, Pilates could be recommended as a complement but not as a replacement for rehabilitation; also, for this reason, we considered it unethical to include patients who should suspend their treatments for the aims of the study. Furthermore, asynchronous telerehabilitation tools for self-administered balance training should be proposed when the patient’s ability to maintain balance safely is preserved (eg, pregnant women will be excluded until after giving birth). In any case, we included patients with preserved balance evaluated with the Berg Balance Scale score >46 [34].

To ensure the ability to use the MS-FIT exergame, normal cognitive functioning determined by a Mini-Mental Status Examination score >24 [35] is required; a Hospital Anxiety and Depression Scale score <10 in the 2 subsets of anxiety and depression [36] could prevent a loss of adherence due to mood disorders.

#### Exclusion Criteria

The study excludes individuals who have received at least 1 rehabilitation treatment (except speech therapy, sphincter rehabilitation, and psychological support) in the last month before being contacted. Other exclusion criteria are visual deficits that could compromise the use of the MS-FIT exergame and relapses in the last 3 months. Participants with relapses during the period of involvement in the study will be considered dropouts.

All hardware and software components will be provided to the participants in the MS-FIT group; training provided by the study manager will ensure ease of use. For this reason, technology will not be an exclusion criterion.

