### Intervention

All participants will be allowed to continue their leisure-time physical activities.

Participants in the MS-FIT group will receive the MS-FIT exergame [28]. They will be required to train at home with MS-FIT for 12 weeks by performing the exercises for a total of 30 minutes/day for at least 3 days/week.

While gaming, participants will choose their favorite and most useful exercises; the difficulty of the exercise will increase based on the user’s performance. In this way, the exercise selection and the reward structure will ensure the personalization of the intervention.

Before starting the intervention, each participant will be trained in the use of the tool by the study manager.

Participants in the control group will not receive MS-FIT; however, as a reward for their participation, we will offer them the MS-FIT intervention at the end of their study involvement.

All participants will be assessed at T0, T1, and T2.

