#### Other Measures

Adherence to the intervention will be provided by the number of sessions actually performed as automatically recorded by the MS-FIT tool and the number of dropouts.

Safety will be assessed by the number of potential issues (ie, number of falls). The severity of adverse events will be graded according to the Common Terminology Criteria for Adverse Events v 4.0 on a 5-point scale (grade 1, mild discomfort; grade 2, moderate discomfort; grade 3, severe inability; grade 4, life-threatening or disabling; grade 5, death) and reported in detail on the eCRF. A grade higher than grade 2 will be considered as a condition for dropout.

We will also collect information on the pharmacological treatments (specific and nonspecific for MS) followed by participants, comorbidities, and the type of PA practiced during participation in the study.

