### Criteria for Premature Withdrawal

In addition to withdrawal of consent at any time, the study manager at each site may also consider as criteria for premature withdrawal any medical conditions that could jeopardize the safety of the patient if she or he continues the study, changes in the disease treatment during the study, and noncompliance of the participants to the study procedures.

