### Statistical Analysis

Descriptive statistics will be used to evaluate differences between the 2 groups of participants. The study hypotheses will be tested using an intention-to-treat analysis, where all consenting patients who were randomized during the accrual period will be included in the analysis.

Continuous data will be summarized using count, mean, median, SD, and IQRs, whereas categorical measures will be described using frequencies. The assumption of normality will be tested with the Shapiro-Wilk test. Pre-post effects within groups will be investigated using the paired *t* test or the Wilcoxon matched-pairs signed-rank test. Between-group proportions will be compared by chi-square or Fisher exact test, while between-group comparisons for continuous variables will be done using either the unpaired 2-sided *t* test or the 2-sided Wilcoxon 2-sample test for nonnormal data. Correlations will be computed using Pearson or Spearman coefficients.

The primary analysis will be performed by comparing mean changes from T0 to T1 in the primary and secondary study outcomes. In particular, the MS-FIT group will be compared with the control group with analyses of covariance. The model includes change as the dependent variable, with the intervention group as the main effect and baseline and number of sessions as additional covariates. Finally, generalized estimating equation models will be performed to assess the persistence of the intervention effect; here the mean effect of the intervention at the time points T0, T1, and T2 on all outcomes, adjusted for the baseline value, will be evaluated between the 2 groups.

Differences in the outcome measures between subgroups defined by different polymorphisms will be analyzed using the analysis of variance or the Kruskal-Wallis test, as appropriate.

Statistical analysis will be performed using STATISTICA 7.1 software (StatSoft GmbH). Significance will be recognized for *P*<.05.

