## Results

Recruitment for the trial started on March 16, 2022, and the first participant was randomized on the same day. As of March 2022, we enrolled 126 participants who received a T0 visit; up to now, 108 received a T1 visit and 103 received a T2 visit. Data analysis and results will be published in early 2025.

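### Relapse and adverse events above grade 2 make randomised participants dropouts, and the protocol does not reconcile this with its intention-to-treat analysis of everyone randomised

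*Protocol article*

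**What the plan says.** Three places in the Methods end participation, or allow it to end, because of something that happens after randomisation:

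- Exclusion Criteria: "Participants with relapses during the period of involvement in the study will be considered dropouts". This is worded as a rule.
- Other Measures, on adverse events: "A grade higher than grade 2 will be considered as a condition for dropout". This is also worded as a rule.
- Criteria for Premature Withdrawal: besides safety-related medical conditions, "the study manager at each site may also consider as criteria for premature withdrawal" the following: "changes in the disease treatment during the study, and noncompliance of the participants to the study procedures". This is discretionary.

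Two other places assume that nobody is lost by design. The Intervention section says "All participants will be assessed at T0, T1, and T2". The Statistical Analysis section announces an intention-to-treat analysis in which "all consenting patients who were randomized during the accrual period will be included in the analysis".

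The primary model needs a T1 measurement: "The primary analysis will be performed by comparing mean changes from T0 to T1 in the primary and secondary study outcomes". It is an analysis of covariance with that change as the dependent variable.

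The Results section reports 126 participants with a T0 visit, of whom so far "108 received a T1 visit and 103 received a T2 visit".

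**The concern.** Intention-to-treat rests on comparing the groups as randomised, whatever happens afterwards. Rules that drop people because of later events work against this when the events are linked to the outcome. Relapse and serious adverse events can plausibly slow the TUG, and a change of disease treatment often follows worsening. They may also be linked to arm: the Introduction expects participants on leisure-time activity alone to worsen through disease progression.

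The discretionary withdrawals add a second route. According to the sections on enrolment and on the intervention, the study manager randomises participants, tells them the result and trains the MS-FIT users. The person deciding on withdrawal therefore knows the allocation.

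If these participants leave before T1, the primary comparison describes those who stayed free of such events and were not withdrawn, although it is reported as a comparison of everyone randomised.

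**Working it through.** The point turns on what a dropout is, so the relevant places are set side by side first.

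**Wording that points to leaving the study**

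1. The relapse rule applies to all participants. Controls receive no MS-FIT during the trial (Study Design, Intervention), so they have no study intervention to stop. For a control, being a dropout can hardly mean anything except leaving the study.
2. The relapse rule stands under Exclusion Criteria, and the Eligibility Criteria section gives limiting confounding as one purpose of those criteria.
3. The section on premature withdrawal speaks of the patient's safety if he or she continues in the study, not in the training.

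**Wording that points to stopping the intervention only**

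1. The Intervention section has all participants assessed at all three time points.
2. Other Measures counts dropouts as part of adherence to the intervention.
3. The Statistical Analysis section includes all randomised patients. No sentence says that assessment of dropouts stops or that their data are left out.

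**Consequence for the primary analysis under each reading**

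| Meaning of dropout | Timing | T0-T1 change available? | All-randomised promise |
|---|---|---|---|
| Stops the intervention, still assessed | any | yes | can be kept |
| Leaves the study | before T1 | no | not met from observed data |
| Leaves the study | between T1 and T2 | yes, T2 lost | can be kept for T1, if the value is used |

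The conflict is therefore confined to the second row. The better-supported reading leads there for every relapse or adverse event above grade 2 before week 12.

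**Extent of missing visits** (inputs from the Results section: 126, 108 and 103)

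- No T1: 126 − 108 = 18, and 18/126 = 14.3%.
- No T2: 126 − 103 = 23, and 23/126 = 18.3%.
- Loss allowed for in the Sample Size section: 15%, and 0.15 × 126 = 18.9 participants.

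The T1 figure is within the planned allowance. The counts are interim, so some visits may be pending. Neither reasons nor arms are given, so none of the 18 can be attributed to these rules.

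**Whether a bias can be derived**

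Let f be the fraction of an arm without T1, and D the amount by which the mean TUG change of those lost is worse than that of those retained. The full-arm mean is the retained mean plus f × D. Before covariate adjustment, the retained-only difference (MS-FIT minus control) is therefore shifted from the full difference by

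f(control) × D(control) − f(MS-FIT) × D(MS-FIT).

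A positive shift works against MS-FIT and a negative one in its favour. The shift is zero when the two products are equal. The document gives none of the four quantities, so neither the sign nor the size follows from it.

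**The case against.** The strongest reply is that the passages can be read together. No sentence excludes dropouts from the analysis, one sentence has everyone assessed three times, and another includes everyone randomised. This stands to the extent that the conflict is a strong tension created by an undefined term. A reader might infer an outright contradiction, or that the announced intention-to-treat analysis is in truth a complete-case analysis. The document does not say so. Handling of missing T1 values may stand in the full protocol or analysis plan, which are not shown, and its absence from an article is not counted here. The reply does not remove the problem: for controls the intervention-only reading of the relapse rule makes little sense, and sites could apply the rule differently.

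Other tempting readings also go too far:

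- **Noncompliance occurs only under MS-FIT.** The criterion concerns study procedures, not training sessions. Controls can breach the ban on exercise and rehabilitation, or miss visits.
- **All four triggers act automatically.** Only relapse and adverse events above grade 2 are worded as rules. Treatment change and noncompliance are at the study manager's discretion.
- **The planned models must be replaced.** Analysis of covariance and generalised estimating equations can both tolerate losses that depend only on arm and baseline included in the model. A repeated-measures model with baseline as covariate gains nothing for someone with neither T1 nor T2.

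**Conclusion.** The concern holds in a limited form. Two mandatory rules and one discretionary provision let post-randomisation events, plausibly related to TUG and possibly to arm, end participation. On the better-supported reading, those affected before T1 have no change score and cannot enter the primary analysis. This does not fit with analysing everyone randomised or with assessing everyone at T0, T1 and T2.

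The conclusion rests on one interpretation: that a dropout leaves the study. If the term means only stopping the intervention, what remains is a definition to be written down.

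The extent is bounded only by the interim counts, 18 of 126 without T1 and 23 of 126 without T2, with reasons, arms and pending visits unknown. Any figure for the bias would rest on assumed rates and is not offered. The matter still needs settling before the data are analysed, because it decides who enters the primary comparison.

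**What to change.** Reconcile Exclusion Criteria, Intervention, Other Measures, Criteria for Premature Withdrawal and Statistical Analysis. The clinical stopping rules need not change and no view is taken on them.

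1. Define dropout, and separate stopping the intervention from leaving the study.
2. Continue T1 and T2 assessment for participants who have not withdrawn consent and can safely be assessed.
3. State that every TUG value obtained is analysed in the randomised arm, including values after a relapse, adverse event, treatment change or noncompliance.
4. Add a sensitivity analysis in which T1 values missing because of relapse or adverse events are imputed as worsened.

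The planned analysis of covariance and estimating-equation models can stay.

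The cost is an amendment to the wording, which under Ethical Considerations needs the investigators' agreement and ethics approval, plus some extra analysis work. Including values after these events may dilute the estimated effect. T1 visits already missed cannot be recovered; for those participants only the sensitivity analysis helps, and it requires the reason for loss to be known.

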### Intervention

All participants will be allowed to continue their leisure-time physical activities.

Participants in the MS-FIT group will receive the MS-FIT exergame [28]. They will be required to train at home with MS-FIT for 12 weeks by performing the exercises for a total of 30 minutes/day for at least 3 days/week.

While gaming, participants will choose their favorite and most useful exercises; the difficulty of the exercise will increase based on the user’s performance. In this way, the exercise selection and the reward structure will ensure the personalization of the intervention.

Before starting the intervention, each participant will be trained in the use of the tool by the study manager.

Participants in the control group will not receive MS-FIT; however, as a reward for their participation, we will offer them the MS-FIT intervention at the end of their study involvement.

All participants will be assessed at T0, T1, and T2.

### Assessment

The assessment will consist of clinical tests measuring the domains most relevant to MS. The primary outcome will always be administered first; the order of the secondary outcomes will be randomized across participants; however, the same order will be maintained for the individual participant. We assume that the administration of all tests will take, on average, about 60 minutes.

Multimedia Appendix 3 summarizes when the different outcome measures should be collected.

#### Primary Outcome

The primary outcome of the study is TUG [37], commonly used to measure dynamic balance and to assess activity limitations by examining the patient’s ability to ambulate and perform transfers. The TUG was originally created to predict the risk of falling in geriatric patients.

At the “go” signal, the participant must rise from a chair, walk 3 m, turn around, return to the chair, and sit down as quickly but safely as possible. The participant starts with the back against the chair and the arms resting on the armrests and is timed from the moment he or she lifts the pelvis from the chair until he returns with the pelvis on the chair [34]. The participant wears his or her regular footwear and uses his or her customary walking aid (none, cane, or walker); however, due to the eligibility criteria adopted in this study, participants will not use assistive devices for walking. No physical assistance is given.

#### Secondary Outcomes

Secondary outcomes will evaluate the effects of the intervention on the following:

Motor function: visual analog scale (VAS; 0-10) for balance subjective disability improvement [38], Timed 25-Foot Walk (T25FW) [39], Ambulation Index [40], 2-minute walk test (2MWT) [41], Twelve Item Multiple Sclerosis Walking Scale (MSWS-12) [42,43], and Nine-Hole Peg Test (9HPT) [44].Cognition: Brief International Cognitive Assessment for Brief International Cognitive Assessment for Multiple Sclerosis (BICAMS), which consists of the Symbol Digit Modalities Test (SDMT), the California Verbal Learning Test-II (CVLT-II), and the Brief Visuospatial Memory Test-Revised (BVMT-R) [45].Fatigue: Modified Fatigue Impact Scale (MFIS) [46,47].QoL: Multiple Sclerosis Quality of Life-54 (MSQoL-54) [48,49].Well-being: Psychological Well-Being Scales (PWB) [50,51].PA: International Physical Activity Questionnaire (IPAQ) [52,53], the Minnesota Leisure-Time Physical Activity Questionnaire [54] which provides a general evaluation of the total energy expenditure in leisure time physical activity.Perceived intervention effect: 7-point Patients’ Global Impression of Change (PGIC; from 1=“no change or worse” to 7=“a great deal better”) scale.

#### Technology

Furthermore, acceptance of the used technology will be evaluated with an ad-hoc questionnaire on patients’ expectations; satisfaction with the intervention will be evaluated with the Client Satisfaction Questionnaire (CSQ-8) [55,56] and the Tele-healthcare Satisfaction Questionnaire (TSQ-WT) [57].

#### Blood Sample

If the participant consents, a peripheral blood sample will be collected at T0 in vacutainer tubes containing ethylenediaminetetraacetic acid. According to previous studies [29], participants will be divided into subgroups with respect to polymorphism. All blood samples will be genotyped for a total of 55 genetic polymorphisms of 23 potential regulators, such as Homer1, AKT1, RAPTOR, D2R, GAPD, CHAT, p53, BRCA2, LIG4, XRCC5, CYP3A4, NBS1, MDM2, CNR1, ATTn, CNR2, GRIN1, GRIN2B, TRPV1, FAAH, COMPT, and BDNF.

For example, CNR1 region containing AAT repetitions will be amplified by polymerase chain reaction from genomic DNA; sequencing products will be purified using a rapid, high-performance dye-terminator removal kit and will be subjected to electrophoresis; AAT repetitions will be counted on the resulting electropherograms (short AAT: homozygous or heterozygous for an allele with ≤11 repeats of AAT triplets; long AAT: homozygous for an allele with ≥12 repeats of AAT triplets). For the TRPV1 and FAAH, the iPLEX Gold technology and MassARRAY high-throughput DNA analysis will be performed.

The blood sample will be collected early in the morning after awakening (8:00 AM). To synchronize the sample with lifestyle variables, participants were requested to avoid excessive physical activity in the last 3 days before blood sampling, to sleep for 7-8 hours the night before the study, to avoid starvation, and to have a normal breakfast in the morning [29]. The samples will be analyzed in the center of DC.

#### Other Measures

Adherence to the intervention will be provided by the number of sessions actually performed as automatically recorded by the MS-FIT tool and the number of dropouts.

Safety will be assessed by the number of potential issues (ie, number of falls). The severity of adverse events will be graded according to the Common Terminology Criteria for Adverse Events v 4.0 on a 5-point scale (grade 1, mild discomfort; grade 2, moderate discomfort; grade 3, severe inability; grade 4, life-threatening or disabling; grade 5, death) and reported in detail on the eCRF. A grade higher than grade 2 will be considered as a condition for dropout.

We will also collect information on the pharmacological treatments (specific and nonspecific for MS) followed by participants, comorbidities, and the type of PA practiced during participation in the study.

### Criteria for Premature Withdrawal

In addition to withdrawal of consent at any time, the study manager at each site may also consider as criteria for premature withdrawal any medical conditions that could jeopardize the safety of the patient if she or he continues the study, changes in the disease treatment during the study, and noncompliance of the participants to the study procedures.

### Sample Size

The sample size was calculated by referring to the TUG change after a Pilates intervention found by Kalron et al [30] in a group of people with MS. The authors found no difference between the group receiving the Pilates intervention and the control group receiving an intervention of physical therapy. The Pilates group improved the TUG performance by about 1.8 seconds, which is clinically relevant for people with MS. Considering a variability of about 3.4 seconds, a power of 80%, a significance level (2-sided) of 5%, and a potential loss of 15% of patients at follow-up, the estimation of the necessary sample size consists of approximately 63 participants for the experimental group (a total of 126).

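### The 63 per arm does not reproduce from the inputs as printed (they give 66–68), and the 1.8 s target is a one-arm pre-post change that implicitly assumes no mean change in controls

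*Protocol article*

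**What the plan says.** The calculation is in Methods, Sample Size. It takes its effect from an earlier Pilates study in people with MS: "The Pilates group improved the TUG performance by about 1.8 seconds, which is clinically relevant for people with MS". Of the same study it reports: "The authors found no difference between the group receiving the Pilates intervention and the control group receiving an intervention of physical therapy". The remaining inputs are the spread ("Considering a variability of about 3.4 seconds"), 80% power, a two-sided 5% level and "a potential loss of 15% of patients at follow-up". The result is given as "the estimation of the necessary sample size consists of approximately 63 participants for the experimental group (a total of 126".

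Three other places bear on this:

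- **Study Design:** a 1:1 superiority trial in which exercise and most rehabilitation are suspended.
- **Statistical Analysis:** the primary comparison is mean change from T0 to T1 between groups, by analysis of covariance with baseline among the covariates.
- **Introduction:** controls are expected to worsen with disease progression, but no amount is given.

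The Results section reports 126 enrolled, of whom "108 received a T1 visit and 103 received a T2 visit" so far.

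**The concern.** There are two separate problems.

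First, every input needed for a two-sample calculation is printed, yet a reader who puts them into the usual formula does not get 63. The stated 80% power and the stated size therefore do not match as written.

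Second, the trial tests a difference between two arms, but the figure used is a change within one arm. A pre-post change equals a between-group difference only if the control mean does not move. If controls improve, for instance through retest effects, the true difference is smaller than the Pilates-type change. If they worsen, it is larger. The section states no assumption about controls. Power depends far more on this than on the few patients at issue in the first problem.

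**Working it through.** **Inputs.** Difference 1.8 s, SD 3.4 s, power 80%, two-sided alpha 5%, loss 15% (Sample Size); allocation 1:1 (Study Design). The article does not say whether 3.4 s is the SD of change or of a single measurement. It is taken here as the SD of the analysed quantity.

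**Evaluable patients per arm.**
n = 2 × (1.960 + 0.8416)² × (3.4 / 1.8)² = 56.01 by the normal approximation. The two-sample t test needs 57.

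**Allowance for 15% loss.**

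| Method | Per arm |
|---|---|
| 56.01 / 0.85 | 65.9, so 66 |
| 57 / 0.85 | 67.1, so 68 |
| 57 × 1.15 (weaker inflation) | 65.6, so 66 |
| 56 × 1.15 (weaker inflation) | 64.4, so 65 |

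With the correct inflation the result is 66–68 per arm, or 132–136 in total. The stated 63 is 3–5 per arm lower.

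**Attempts to reach 63 with other formulas on the printed inputs.** A one-sided test gives 52–53 per arm after loss. A one-sample or paired formula gives 28 before loss. A Wilcoxon efficiency of 0.955 gives about 70 after loss. None gives 63.

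**What does give 63.**

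- 10% loss instead of 15%: 57 × 1.10 = 62.7, or 57 / 0.90 = 63.3.
- SD 3.3 s: 53 / 0.85 = 62.4, so 63.
- Rounding: 1.84 s with SD 3.40 s gives 2 × (2.8016 × 3.40 / 1.84)² = 53.6, and 53.6 / 0.85 = 63.1. Both values would print as 1.8 and 3.4.
- Baseline adjustment with an assumed correlation of 0.2 between change and baseline: 56.01 × (1 − 0.04) / 0.85 = 63.3.

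**Power at the stated size.** 63 × 0.85 = 53.55 evaluable per arm. The standard error of the difference is 3.4 × √(2 / 53.55) = 0.657 s. By the normal approximation, 1.8 / 0.657 − 1.960 = 0.78, which is 78.2% power. The t test gives 77.5%. If the 108 T1 visits are split evenly (an assumption), 54 per arm gives 77.8% by t test, and the difference detectable with 80% power is 1.85 s.

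**Sensitivity to control change.** Suppose MS-FIT patients change by 1.8 s as in the source arm. The between-group difference is then 1.8 s minus any control improvement, or plus any control worsening. The control changes below are assumptions, because the article gives no figure. Power is by t test with 54 per arm and SD 3.4 s (standard error 0.654 s).

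| Assumed control change | Difference | Power |
|---|---|---|
| improves 0.9 s | 0.9 s | 28% |
| improves 0.6 s | 1.2 s | 44% |
| improves 0.3 s | 1.5 s | 62% |
| none | 1.8 s | 78% |
| worsens 0.3 s | 2.1 s | 89% |
| worsens 0.6 s | 2.4 s | 95% |

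**The case against.** The strongest reply on the arithmetic is that the section presents both inputs and result as approximate. Unrounded values that print identically do give 63, so a calculation error is not established. The primary analysis is also adjusted for baseline. With a correlation of only 0.3 between change and baseline (assumed), 63 per arm with 15% loss would have about 81% power. Both arguments stand. They limit the point to this: 63 does not reproduce from what is printed, and 77.5–78% is the power of an unadjusted comparison, not of the planned model.

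On the effect size, the reply is that the origin of 1.8 s is openly disclosed, that it is called clinically relevant and so can serve as a target, and that controls here are expected to worsen. If they do, assuming no control change is conservative. This also stands in part, but the expected worsening is not quantified and the Sample Size section does not use it.

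Two stronger readings are tempting, and the documents support neither:

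- A reader might infer from the source study's null comparison that 1.8 s cannot be reached here. That comparator was active physical therapy. Controls in this trial have leisure-time activity only, so the null result does not carry over.
- A reader might infer that the trial is seriously underpowered and that a null result would be misread for that reason. A shortfall of about 2 percentage points, or 0.05 s in the detectable difference, does not support this.

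**Conclusion.** The point holds in a limited form. From the inputs as printed, 66–68 per arm are needed rather than 63, and the stated size gives about 77.5–78% power in an unadjusted comparison instead of 80%. This rests on reading 3.4 s as the SD of the analysed quantity and on 15% loss in each arm. The discrepancy is minor and may be no more than rounding.

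The more consequential part is the unstated assumption of zero mean change in controls. A shift of 0.3 s in the control mean changes power by 11 to 16 percentage points (78% to 89% or to 62%), much more than the arithmetic gap does. The documents do not settle which way controls will move, so the assumption should be stated and examined in both directions. It should not be presumed too optimistic.

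**What to change.** Leave the enrolment of 126 as it is and correct the text.

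1. Restate the size and power, for example: *126 randomised, about 107 evaluable at T1 (126 × 0.85), gives about 78% power in an unadjusted comparison for an assumed between-group difference of 1.8 s (SD 3.4 s), or 80% for about 1.85 s.* Alternatively, keep 63 per arm and 80%, and give the unrounded inputs, the type of SD or the baseline correlation that lead to it.
2. State that 1.8 s is a within-group change adopted as a clinically relevant between-group target, on the assumption of no mean change in controls.
3. Show power for differences below and above 1.8 s, as in the table above.
4. Say that the TUG result will be interpreted by the 95% confidence interval of the between-group difference, read against 1.8 s.

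The cost is a few sentences and one small table. Design, enrolment and data collection do not change. Under the first option in step 1, the stated power becomes slightly less favourable.
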